### Outcome Measures

The primary variable of efficacy of the study will be the score of HAMD-17 obtained by the blind assessors before and after treatment. A full response is considered if the decline in scores on the HAMD-17 is greater than 50%, and a partial response if the reduction is between 25% and 50%. We will use BDI-21, filled out by the patient, and also the self-administered SF-36 and the GCI as secondary efficacy measures.

### Power calculation

To estimate the sample size, HAMD-17 final score was used. The value expected for control group is 12 (SD: 8) and the value expected for active treatment group is 8 (SD: 6). An alpha error of 5% is assumed and a beta error rate of 20% is accepted. The final sample is 34 for both samples. Expecting a 15-20% loss, the necessary sample size will be 40 patients in each group, constituting thus a total sample of 80 patients.

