### Statistical Analyses

Obtained data will be analyzed with the Statistical Package for the Social Sciences (SPSS) version 17. There will be a descriptive analysis of baseline variables by comparing these variables between the groups. We will examine the outcome variables using the Student t-Fisher as mean comparison test. We will also use the analysis of variance (ANOVA) repeated means, the Mann-Whitney for comparisons involving ordinal variables and the Chi-square test for categorical variables. For the multivariate analysis linear and logistic regression models will be used.

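### The HAMD-17 contrast that decides the trial is not fixed: the outcome, sample size and analysis sections point to different ones

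*Protocol article*

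**What the plan says.** Three sections of the protocol article bear on this.

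- **Outcome Measures:** "The primary variable of efficacy of the study will be the score of HAMD-17 obtained by the blind assessors before and after treatment". The next sentence adds a categorical version on the same scale: "A full response is considered if the decline in scores on the HAMD-17 is greater than 50%, and a partial response if the reduction is" from 25% to 50%. The section then lists its secondary measures, the BDI-21, "and also the self-administered SF-36 and the GCI as secondary efficacy measures". HAMD-17 response is not on that list and is not called primary either.
- **Power calculation:** "To estimate the sample size, HAMD-17 final score was used". The expected values are 12 (SD 8) for control and 8 (SD 6) for active treatment, with one alpha of 5% and a beta of 20%.
- **Statistical Analyses:** a Student t-test is to be used on the outcome variables. Then: "We will also use the analysis of variance (ANOVA) repeated means", with Mann-Whitney for ordinal variables, chi-square for categorical ones, and linear and logistic regression for multivariate analysis. No test is singled out for the primary variable.

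The study schedule (Table 1) has HAMD-17 at baseline and week 24 only.

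**The concern.** A score taken before and after treatment is two measurements, not yet a comparison. It can be analysed as the final score, as the change, as a group-by-time effect, or as the final score adjusted for baseline. The sample size section uses one of these, the final score. The analysis section supplies methods for more than one and does not choose.

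With about 34 to 40 patients per arm, a chance imbalance in baseline HAMD-17 is likely. Final score and change can then fall on opposite sides of p = 0.05. The single 5% alpha used for sizing holds only if one contrast is named in advance. The planned power also refers to the final score alone, and change has a different variance.

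**Working it through.** **1. The sections side by side.**

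| Section | Quantity | Method |
|---|---|---|
| Outcome Measures | HAMD-17 before and after; response defined but unranked | none given |
| Power calculation | HAMD-17 final score | two means, alpha 5% |
| Statistical Analyses | the outcome variables in general | t-test; also repeated-measures ANOVA and others |

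With two visits, the group-by-time test of a repeated-measures ANOVA is the same test as a t-test on change (F = t²). The analysis section therefore offers both a final-score test and a change test of the primary variable.

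**2. The plan's own figure.** The sizing inputs give n per arm = 2(1.96 + 0.842)² × SD² / difference², with SD² = (8² + 6²)/2 = 50 and difference 4. This is 2 × 7.85 × 50 / 16 = 49.1, so 50 per arm two-sided (39 one-sided). The stated 34 is not reproduced; SD 6 in both arms comes nearest, at 36. That is a separate point. It matters here only because the power statement is not secure even for the final score.

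**3. Final score or change, no treatment effect.** Assumed, because the document does not give them: baseline SD 5 and baseline-final correlation r from 0 to 0.6. The final SD is 8 in both arms, the stated control value.

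- SD of change = √(5² + 8² − 2·r·5·8)
- Correlation between the two test statistics = (8 − 5r) / SD of change
- Chance that at least one has p < 0.05 = 1 − P(|Z1| < 1.96 and |Z2| < 1.96), bivariate normal with that correlation

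| r | SD of change | Correlation of tests | Either p < 0.05 | Residual variance after baseline adjustment (1 − r²) |
|---|---|---|---|---|
| 0 | 9.43 | 0.848 | 7.5% | 1.00 |
| 0.2 | 8.54 | 0.819 | 7.7% | 0.96 |
| 0.4 | 7.55 | 0.795 | 7.8% | 0.84 |
| 0.6 | 6.40 | 0.781 | 7.9% | 0.64 |

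Simulation under no effect (10,000 trials per scenario, 34 or 40 per arm) gave 7.7-9.1% over a wider set: baseline 20 (SD 5) or 22 (SD 6), final SD 7 or 8, r from 0 to 0.8.

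The table also shows the effect on power. Change is less precise than the final score when r is below 5/(2 × 8) = 0.31 and more precise above it.

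**4. Adding response above 50% by chi-square.** In the same simulations, at least one of final score, change and response reached p < 0.05 in 9.8-11.6% of trials. Three independent tests would give 1 − 0.95³ = 14.3%. The observed figure is lower because the three are correlated.

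**5. One named contrast.** Tested alone, each stayed close to 5%: final score 4.6-5.5%, change 4.4-5.6%, baseline-adjusted model 4.6-5.6% (Monte Carlo standard error about 0.3 points).

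**The case against.** The strongest reply is that the article names one primary variable, the blind-rated HAMD-17 score, and that before and after merely describes the two visits. The t-test comes first in the analysis section, Mann-Whitney and chi-square are tied to ordinal and categorical variables, and other outcomes such as the GCI and work status could be what those tests are for. Under randomisation the expected between-arm difference is the same for final score and for change, so the two do not estimate different effects. Finally, this is a journal article, and the decisive model may well be set out in a full protocol or analysis plan that is not shown.

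Much of this stands. The equality of expected differences is correct: the issue with that pair is variance and choice, not a different question. The absence of a detailed model or a multiplicity rule is not held against the article. What remains is that the article does state a primary variable, a sizing variable and a list of tests, and these do not identify one contrast. Repeated-measures ANOVA is a real second route for the same score, and response is left without a rank.

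A reader might go further and infer that the primary variable is defined three ways, that the trial may succeed on any of them, and that its type I error is therefore 11%. The document does not support this. Response is never called primary, no sentence makes a positive result on any version sufficient, and the only alpha given is the one used for sizing. The 11% describes an assumed rule, not the stated plan.

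**Conclusion.** The point holds as a failure to fix one primary contrast across Outcome Measures, Power calculation and Statistical Analyses. The inflation is conditional. If the contrast were picked after the results were known, type I error would be roughly 7-9% for final score or change and about 10-12% with response above 50% added, against 5% for one pre-named test. These ranges rest on an assumed baseline of 20 (SD 5), a final score of 12 (SD 8) in both arms and a correlation of 0 to 0.6. They move little across the other values tried. Only the final mean and SD come from the document, as the control-group expectation.

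**What to change.** Reconcile the three sections so that they name the same contrast:

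- **Outcome Measures:** make the week-24 HAMD-17 score, the variable used for sizing, the single primary endpoint. Label change from baseline, full response and partial response as secondary or supportive.
- **Statistical Analyses:** name one primary test, a linear model for week-24 HAMD-17 with treatment arm and baseline HAMD-17 as terms, at two-sided 5%. Give the t-test and repeated-measures ANOVA a supportive role if they are kept.

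This holds type I error at 5%. With baseline-final correlation r, it cuts the residual variance by the factor 1 − r², for example to 0.84 at r = 0.4. The cost is about two sentences: baseline HAMD-17 is already collected and linear regression is already listed. The change should be made before outcome data are examined by arm.

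### The 34 patients per arm do not follow from the stated inputs: 12 (SD 8) versus 8 (SD 6) needs about 50 evaluable per arm two-sided, so unadjusted power is about 60–65%, not 80%

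*Protocol article*

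**What the plan says.** The Power calculation section of the protocol article contains the whole derivation.

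- Endpoint: "To estimate the sample size, HAMD-17 final score was used".
- Expected values: "The value expected for control group is 12 (SD: 8) and the value expected for active treatment group is 8 (SD: 6".
- Error rates: "An alpha error of 5% is assumed" and "a beta error rate of 20% is accepted". The section does not say whether the test is one- or two-sided.
- Result: "The final sample is 34 for both samples".
- Allowance for loss: "Expecting a 15-20% loss, the necessary sample size will be 40 patients in each group", for a total of 80.

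No baseline correlation or covariate adjustment enters the calculation. Statistical Analyses names a Student t-test for comparing means, and also lists repeated-measures ANOVA and regression models. Outcome Measures makes HAMD-17 the primary efficacy variable.

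**The concern.** The paragraph states every input that a two-sample comparison of means needs, so its result can be checked directly. A 4-point difference against SDs of 8 and 6 is a standardised effect of about 0.57, and 34 per arm is clearly too few for 80% power at that effect.

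This paragraph is the only justification given for 80 patients. If the figure is wrong, the trial claims a 20% chance of missing its planned effect on the primary outcome when the real chance, on its own assumptions, is well above that. A non-significant result could then be given more weight as evidence against the recommendations than the design supports.

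**Working it through.** **Inputs** (all from Power calculation): difference 12 − 8 = 4; SDs 8 and 6; alpha 5%; power 80%; equal arms; loss 15–20%. Two-sided testing is assumed first because the document does not say.

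**Is 34 per arm or in total?** The next sentence inflates it to 40 in each group, and 34/0.85 = 40.0, so it is per arm. Read as a total (17 per arm), it would give power of only about 36–38%.

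**Attempt to reproduce 34.** The formula is n per arm = (z₁₋α/₂ + z₁₋β)² × (SD₁² + SD₂²) / difference².

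| Reading | Calculation | n per arm |
|---|---|---|
| Both stated SDs, two-sided | (1.960 + 0.8416)² × (64 + 36)/16 = 7.849 × 6.25 = 49.06 | 50 (51 with t) |
| Both stated SDs, one-sided | (1.645 + 0.8416)² × 6.25 = 38.6 | 39 (40 with t) |
| SD 8 in both arms, two-sided | 7.849 × 128/16 = 62.8 | 63 |
| SD 6 in both arms, two-sided | 7.849 × 72/16 = 35.3 | 36 |

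No row gives 34. Solving backwards, a two-sided n of 34 needs a common SD of 4 / [√(2/34) × 2.8016] = 5.89. The nearest row is the one that uses the active-arm SD for both arms and leaves out the control SD of 8.

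**Power for a 4-point difference with the stated SDs.** The standard error is √(100/n). Two-sided power by the normal approximation is Φ(4/SE − 1.960). The t column uses the noncentral t distribution (Welch).

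| Evaluable per arm | SE | Two-sided, normal | Two-sided, t | One-sided, normal |
|---|---|---|---|---|
| 32 | 1.768 | 61.9% | 60.4% | 73.2% |
| 34 | 1.715 | 64.5% | 63.1% | 75.4% |
| 40 (no loss) | 1.581 | 71.6% | 70.4% | 81.2% |

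**Difference detectable with 80% power, two-sided.** This is 2.8016 × SE: 4.80 points at 34 per arm and 4.95 at 32. With the t distribution it is 4.88 and 5.03, so about 4.9 and 5.0.

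**Allowance for loss.** 34/0.85 = 40.0, but 34/0.80 = 42.5. From 40 per arm, a 20% loss leaves 40 × 0.80 = 32.

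**Size that the stated inputs require.** From 50 per arm: 50/0.85 = 58.8 and 50/0.80 = 62.5, so 59–63. From 51 (t): 51/0.85 = 60 and 51/0.80 = 63.75, so 60–64. The total is about 118–128, against 80 planned.

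**Baseline adjustment.** Adjusting for baseline HAMD-17 multiplies the required n by (1 − r²), where r is the correlation between baseline and final score. Setting 49.06 × (1 − r²) = 34 gives r = 0.55; with the t distribution r is about 0.57. The document gives no value for r.

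**The case against.** Four counter-arguments deserve a hearing.

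1. *Sidedness is not stated.* This is true, and the 60–65% figure is a two-sided one. At one-sided 5%, power with 34 per arm is about 75%, and about 81% if all 40 are followed. But 34 still falls short of the 39 required, so the error does not depend on this choice.

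2. *An adjusted analysis could recover the power.* Outcome Measures refers to scores before and after treatment, and the analysis section lists repeated-measures ANOVA and linear regression. With an assumed correlation of 0.5, an adjusted analysis at 34 per arm would have about 76–77% power, and with 0.57 about 80%. This stands as a caution against calling the trial's power 60–65% whatever the analysis. It does not rescue the calculation, which is explicitly based on the final score and uses no correlation.

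3. *The loss step fits a simple add-on.* 34 × 1.15 = 39.1 and 34 × 1.20 = 40.8, so 40 lies within that range. Even on that convention, 40 is below the figure for 20% loss. The shortfall is small and secondary to the gap between 34 and 50.

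4. *The source of the error is a guess.* That is fair. Using SD 6 in both arms gives 36, not 34. Omission of the control SD is a plausible explanation but is not shown, and the finding does not rest on it.

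**Conclusion.** The stated sample size is wrong as written. With the plan's own means, SDs and error rates, 80% power needs 50–51 evaluable patients per arm two-sided, or 39–40 one-sided; 34 meets neither. For an unadjusted two-sided 5% comparison of final scores, the risk of missing the planned 4-point difference is 35–37% at 34 per arm and 38–40% at 32, not 20%. The 40 per arm covers a 15% loss but not 20%. These figures assume that the stated means and SDs are the intended ones and that the final scores are compared without baseline adjustment, as the power paragraph implies.

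**What to change.** Keep 80 patients and replace the power paragraph with text along these lines:

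> With 80 patients randomised and 15–20% loss (32–34 evaluable per arm), an unadjusted comparison at two-sided 5% has about 60–65% power for final HAMD-17 scores of 12 (SD 8) versus 8 (SD 6), and 80% power for a difference of about 4.9–5.0 points. Forty per arm allows for a 15% loss.

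If a one-sided test was intended, say so and give the corresponding power (about 75% at 34 per arm). If the primary analysis will adjust for baseline HAMD-17, state that and give power across a range of assumed baseline–final correlations, noting that about 0.57 is needed for 80% at 34 per arm. If a different control SD was intended, correct it and redo the calculation.

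The cost is the rewording of one paragraph and a less favourable stated power. No extra patients are needed, and the design and procedures do not change.

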### Statistical Analyses

Obtained data will be analyzed with the Statistical Package for the Social Sciences (SPSS) version 17. There will be a descriptive analysis of baseline variables by comparing these variables between the groups. We will examine the outcome variables using the Student t-Fisher as mean comparison test. We will also use the analysis of variance (ANOVA) repeated means, the Mann-Whitney for comparisons involving ordinal variables and the Chi-square test for categorical variables. For the multivariate analysis linear and logistic regression models will be used.

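### The plan does not tie the primary HAMD-17 comparison to a baseline-adjusted model, although HAMD-17 is rated on everyone before randomisation

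*Protocol article*

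**What the plan says.** - **Primary variable.** Outcome Measures: "The primary variable of efficacy of the study will be the score of HAMD-17 obtained by the blind assessors before and after treatment".
- **Timing.** The section on trial procedures and its Table 1 place the blind HAMD-17 rating at the baseline visit, before allocation, and again at week 24. BDI-21 and SF-36 are completed at the screening visit and at week 24.
- **Tests.** Statistical Analyses: "We will examine the outcome variables using the Student t-Fisher as mean comparison test", and then "We will also use the analysis of variance (ANOVA) repeated means". Mann-Whitney is assigned to ordinal variables and chi-square to categorical ones. Linear and logistic regression appear in the last sentence, for multivariate analysis, with no covariates and no link to the primary variable. No method is marked as primary.
- **Sizing.** Power calculation: "To estimate the sample size, HAMD-17 final score was used". The expected final scores are 12 (SD 8) in the control arm and 8 (SD 6) in the active arm. On error rates: "An alpha error of 5% is assumed and a beta error rate of 20% is accepted". No baseline SD and no correlation between visits is given.

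**The concern.** With one score before randomisation and one at week 24, the two named tests use the baseline either not at all or inefficiently. A t-test on the final score ignores it. The group-by-time term of a two-visit repeated-measures ANOVA is the same test as a t-test on the change score, which subtracts the whole baseline value whether or not it predicts the outcome that strongly. A linear model with baseline as covariate estimates how much to subtract.

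The trial has little precision to spare. On its own inputs it needs about 50 evaluable patients per arm, against the 34 stated. Naming several methods without ranking them also leaves open which result will count as the trial's answer.

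**Working it through.** **Inputs.** From Power calculation: difference 12 − 8 = 4; SDs 8 and 6; alpha 5%; beta 20%; 34 evaluable, read as per arm because 34/0.85 = 40. Assumed: a two-sided test (sidedness is not stated), and a correlation r between baseline and final score, the same in both arms. Neither r nor the baseline SD is in the document, so both are varied.

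**Plan's own figure.** Pooled SD = √((64 + 36)/2) = 7.07. The normal-approximation sample size is 2 × (7.07 × (1.96 + 0.84)/4)² ≈ 49.1, so 50 per arm (51 with the noncentral t). The stated 34 does not reproduce. That is a separate fault; 34 is used below because it is what the plan expects to have.

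**Final-score t-test.** SE = 7.07 × √(2/34) = 1.715. Noncentrality = 4/1.715 = 2.332 on 66 df. Power = 63.2% (64.5% by normal approximation).

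**ANCOVA.** The residual SD is 7.07 × √(1 − r²), so the noncentrality becomes 2.332/√(1 − r²) on 65 df.

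**Change score (group-by-time).** Variance = SD_post² + SD_pre² − 2·r·SD_pre·SD_post. This can be rewritten as

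SD_post²(1 − r²) + (SD_pre − r·SD_post)².

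The first term is the ANCOVA variance and the second cannot be negative. So the change score is never more efficient than ANCOVA (one degree of freedom aside), and it equals ANCOVA only when SD_pre = r·SD_post. It is worse than the plain final score when r < SD_pre/(2·SD_post). That threshold is 0.5 if the two SDs are equal, and 5/(2 × 7.07) = 0.35 if the baseline SD is 5.

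Power at 34 per arm, noncentral t:

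| Assumed r | Final-score t-test | ANCOVA | Change score, SD_pre = 7.07 | Change score, SD_pre = 5 |
|---|---|---|---|---|
| 0.3 | 63% | 67% | 49% | 60% |
| 0.4 | 63% | 71% | 56% | 66% |
| 0.5 | 63% | 76% | 63% | 73% |
| 0.6 | 63% | 82% | 73% | 81% |

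**Share of the shortfall recovered.** The shortfall from 80% is 80 − 63.2 = 16.8 points. ANCOVA recovers (67.3 − 63.2)/16.8 = 24% of it at r = 0.3, (70.8 − 63.2)/16.8 = 45% at 0.4, (75.6 − 63.2)/16.8 = 74% at 0.5, and all of it at 0.6. The correlation needed for 80% power is 0.57 with the noncentral t and 0.55 with the normal approximation. With 32 per arm (20% loss from 40) it is 0.61.

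**The case against.** The strongest reply is that nothing here is an error. Under randomisation the t-test is a valid comparison, and it matches the final-score sizing. Linear regression is already on the list of methods, so baseline adjustment is not excluded, and an article may leave covariate lists to a fuller plan. All of this stands as far as it goes. But the article does assign the outcome variables to named tests, and its regression sentence is not tied to the primary comparison. That regression could equally serve the secondary goal of finding which patient characteristics influence effectiveness.

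Several stronger readings are tempting and are not supported:

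- *ANCOVA would recover much of the missing power.* This depends on r, which the document does not give. At r = 0.3 only about a quarter of the shortfall is recovered.
- *The repeated-measures ANOVA is always worse than the t-test when r is below 0.5.* This needs equal SDs at both visits. With a smaller baseline SD the threshold falls, and the change score can come close to ANCOVA.
- *The ANOVA would be judged on its group main effect, which dilutes the difference.* The plan does not say so. An outcome defined before and after treatment points rather to the group-by-time term.
- *The diagnostic mix makes large chance imbalance likely.* Mixed diagnoses may widen the baseline spread, but imbalance in SD units depends on sample size.
- *Baseline adjustment makes up for the sample-size error.* It does not correct that calculation.

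**Conclusion.** The point holds as an improvement in efficiency and pre-specification, not as a claim that the named tests are invalid. The plan leaves the primary HAMD-17 comparison to an unadjusted t-test and a repeated-measures ANOVA, with no ranking between them and no use of baseline HAMD-17 as a covariate.

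The preference for ANCOVA does not depend on r: apart from one degree of freedom, it is at least as precise as either named test. The size of the gain does depend on r. It is about 4 points of power at r = 0.3, 12 at 0.5 and 19 at 0.6, starting from 63%. These figures rest on the protocol's means and SDs, 34 evaluable patients per arm, a two-sided 5% level and a common correlation in both arms. The change-score figures rest also on the assumed baseline SD.

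**What to change.** Add one sentence to Statistical Analyses, for example: *The primary analysis is a linear model of week-24 HAMD-17 on treatment arm with baseline HAMD-17 as a pre-specified covariate, reported as the adjusted mean difference with its 95% confidence interval.*

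Use the same form for BDI-21 and SF-36, each with its own baseline. Keep the t-test and the repeated-measures ANOVA as supportive analyses only. The clinical impression ratings can stay with the method already assigned to ordinal variables.

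The cost is one degree of freedom. No new data, visits or software are needed. Any restatement of power should give the assumed correlation and a range around it, and the Power calculation must still be corrected in its own right.

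### The planning SDs differ between arms (8 and 6), yet the test named for comparing means is Student's t-test, which usually assumes one common variance; naming Welch's version in advance is a free improvement.

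*Protocol article*

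**What the plan says.** The Outcome Measures section makes the HAMD-17 score, rated before and after treatment, the primary efficacy variable. The Power calculation section bases the sample size on the final score: "The value expected for control group is 12 (SD: 8"), and "the value expected for active treatment group is 8 (SD: 6"). It adds "Expecting a 15-20% loss" and arrives at 40 patients per arm, 80 in all.

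For the comparison of means, the Statistical Analyses section states: "We will examine the outcome variables using the Student t-Fisher as mean comparison test". It also lists repeated-measures ANOVA, Mann-Whitney and chi-square tests, and linear and logistic regression for the multivariate analysis. It does not say whether variances are taken as equal, does not mention pooling, and does not exclude an unequal-variance version of the t-test.

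**The concern.** The planning variances are 64 and 36, a ratio of 1.8. The two-sample test that ordinarily goes by Student's name estimates one common variance, so its usual assumption conflicts with the plan's own figures.

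The conflict matters only when the arms also differ in size. The pooled variance gives more weight to the larger arm. If control, the arm with the larger planned spread, loses more patients, the pooled standard error is too small and the interval too narrow. If the active arm loses more, the standard error is too large and power is given away. Blocked randomisation balances the numbers entered, not the numbers who return at six months. The precision attached to the main result would therefore depend partly on which arm lost more patients.

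**Working it through.** **Inputs.** From the Power calculation section: control SD 8, active SD 6, difference 12 − 8 = 4 points, alpha 5% (sidedness not stated; two-sided is used here unless noted), power 80%, 40 randomised per arm, 15-20% loss. The splits of completers between arms are my assumption; the article gives none.

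**The plan's own figure.** The stated number, 34, is read as per arm because 34/(1 − 0.15) = 40. With both SDs, the normal-approximation size per arm is (64 + 36)(z₁ + z₂)²/4²:
- two-sided: 100 × (1.960 + 0.842)²/16 = 49.1, so 50;
- one-sided: 100 × (1.645 + 0.842)²/16 = 38.6, so 39.

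Neither gives 34. That is a separate matter and lends no support to this point. Its relevance here is that two-sided power with 34 per arm is only about 63%, so there is little to spare.

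**Standard errors.** For n₁ control and n₂ active completers:
- pooled variance = [(n₁ − 1)·64 + (n₂ − 1)·36]/(n₁ + n₂ − 2);
- pooled SE = √[pooled variance × (1/n₁ + 1/n₂)];
- true SE = √(64/n₁ + 36/n₂).

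With 68 completers in total (15% loss):
- 34/34: pooled variance (33×64 + 33×36)/66 = 50.00; pooled SE 1.715; true SE 1.715; ratio 1.000.
- 32/36: (31×64 + 35×36)/66 = 49.15; 1.703 against 1.732; ratio 0.983.
- 28/40: (27×64 + 39×36)/66 = 47.45; 1.697 against 1.785; ratio 0.951.
- 40/28: (39×64 + 27×36)/66 = 52.55; 1.786 against 1.699; ratio 1.051.

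**Coverage and power.** These come from simulation with normal data, SDs 8 and 6, and a two-sided 5% level, with millions of draws per setting for coverage and at least 500,000 for power. Coverage of the 95% interval does not depend on the size of the true difference.

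| Completers, control/active | Coverage, pooled | Coverage, Welch | Power for 4 points, pooled | Power, Welch |
|---|---|---|---|---|
| 34/34 | 95.0% | 95.0% | 63% | 63% |
| 32/36 | 94.6% | 95.0% | 64% | 62% |
| 28/40 | 93.8% | 95.0% | 64% | 59% |
| 40/28 | 96.0% | 95.0% | 60% | 64% |

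In the 32/36 and 28/40 rows the higher pooled power is not a real gain: it comes from an interval that is too narrow.

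**How much imbalance to expect.** Suppose both arms have the same loss rate and patients drop out independently. The gap in completers then has SD √(2 × 40 × 0.15 × 0.85) = 3.2 at 15% loss and √(2 × 40 × 0.20 × 0.80) = 3.6 at 20%. The median absolute gap is about 0.67 times that, roughly 2 patients. A gap of 4 (32/36) already makes the standard error wrong by less than 2%, so chance imbalance matters little. The 28/40 and 40/28 settings need all 12 losses in one arm.

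**Cost of Welch's test when completers are equal.** At 34/34 the standard error is identical, and the Welch degrees of freedom at the planning SDs are 33 × 100²/(64² + 36²) = 61.2 against 66. Power changes by about 0.1 percentage points.

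**The case against.** The best defence is that the article does not commit to pooling. It names the test in a few words, and the choice of version is the kind of detail that a condensed article leaves to the full protocol or analysis plan. This stands in part. A reader might infer that the plan fixes a pooled-variance analysis, but the text does not say so. What remains is a named test whose ordinary meaning carries an assumption that the plan's own SDs contradict.

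Second, the smaller SD is paired with the hoped-for mean of 8. A reader might take 100% minus the coverage figures as type I error rates, giving about 6.2% at 28/40 and 4.0% at 40/28. That holds only if the spreads differ in the same way when the advice has no effect, and nothing in the article says they would. With equal spreads the pooled test keeps its level at any split. This objection stands for type I error, but it does not touch coverage and power under the effect the trial is planned to find.

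Third, no section predicts different loss by arm. Both arms follow the same visit schedule, and each patient receives one sheet in an identical-looking envelope. The active advice is more demanding, but any effect of that on retention is conjecture. This stands too. Unequal loss is a possibility that the design does not exclude, not something it implies.

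**Conclusion.** The point holds as a minor one. The planning SDs and the usual assumption of the named test do not agree. The consequence is nil with equal completers, about 2% in the standard error at 32/36, and about 5% if all of a 15% loss falls in one arm. Coverage then runs from about 93.8% to 96%, and at 40/28 the pooled test gives up about 4 percentage points of power. These figures rest on three assumptions: normal scores, SDs of 8 and 6 as planned, and the pooled form of the test.

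The documents do not support saying that the p-value is wrong whenever the arms lose different numbers, or that the type I error is inflated. The first overstates an effect that is slight at likely imbalances. The second needs unequal spreads under no effect, which is not stated. The reason to act is that the change costs almost nothing and removes the dependence on how the loss happens to fall.

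**What to change.** In the Statistical Analyses section, state that between-arm comparisons of means use the unequal-variance (Welch) t-test and report its 95% confidence interval. Fix this before any outcome data are seen, and do not make it conditional on a preliminary test of equal variances.

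The change is one sentence and leaves the sample size as it is. With equal completers about five degrees of freedom are lost and the standard error is unchanged. Robust standard errors for the regression models need not be required on this ground, since the section lists regression for the multivariate analysis and does not tie it to the primary arm comparison.
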